## Abstract

**Purpose:**

Treatment of typical atrial flutter (AFL) with cavo-tricuspid isthmus (CTI) ablation is associated with a high occurrence rate of new onset atrial fibrillation (AF) during follow-up. There are data to support the addition of pulmonary vein isolation (PVI) to CTI ablation in patients with both AF and AFL, but the role of cryoballoon PVI only, with no CTI ablation, in AFL patients with no prior documentation of AF has not been studied.

**Methods:**

CRAFT is an international, prospective, randomised, open with blinded assessment, multicentre superiority study comparing radiofrequency CTI ablation and cryoballoon PVI in patients with typical AFL. Participants with typical AFL are randomised in a 1:1 ratio to either treatment arm, with patients randomised to PVI not receiving CTI ablation. Post-procedural cardiac monitoring is performed using an implantable loop recorder. The primary endpoint is time to first recurrence of sustained symptomatic atrial arrhythmia. Key secondary endpoints include (1) total arrhythmia burden at 12 months, (2) time to first episode of AF lasting ≥ 2 min, (3) time to recurrence of AFL or AT and (4) procedural and fluoroscopy times. The primary safety endpoint is the composite of death, stroke/transient ischaemic attack, cardiac tamponade requiring drainage, atrio-oesophageal fistula, requirement for a permanent pacemaker, serious vascular complications requiring intervention or delaying discharge and persistent phrenic nerve palsy lasting > 24 h.

**Conclusion:**

This study compares the outcomes of 2 different approaches to typical AFL—the conventional ‘substrate’-based strategy of radiofrequency CTI ablation versus a novel ‘trigger’-based strategy of cryoballoon PVI.

**Trial registration:**

(ClinicalTrials.gov ID: **NCT03401099**)

**Electronic supplementary material:**

The online version of this article (10.1007/s10840-020-00746-6) contains supplementary material, which is available to authorized users.

## Background

Typical atrial flutter (AFL) is a macro-reentrant tachycardia with a circuit within the right atrium involving the cavo-tricuspid isthmus (CTI) as the critical isthmus. In patients with AFL, the use of anti-arrhythmic drugs (AADs) to maintain sinus rhythm has limited success [1]. Radiofrequency ablation (RFA) of the CTI has a very high acute success rate and is often used as first line treatment. However, as many as half of these patients go on to develop atrial fibrillation (AF) during follow-up [2, 3]. The elevated risk of AF among patients with AFL indicates the presence of shared underlying disease processes that remain unchanged with only CTI ablation. In fact, there is evidence to suggest that pulmonary vein (PV) ectopy is a common initiating trigger for both arrhythmias [4, 5].

Previous studies have demonstrated the benefit of a combined pulmonary vein isolation (PVI) and CTI ablation approach among patients with AFL [6–8]. A small single centre study even showed the efficacy of standalone PVI in patients with typical AFL compared with AADs or CTI ablation [1]. Despite this, CTI ablation has remained the preferred option for patients with typical AFL, partly because of the perceived complexity of traditional PVI with RFA, and the high possibility of requiring multiple procedures to achieve durable PVI [1]. As such, in spite of the recognition that CTI ablation often represents only a short-term or partial solution, it continues to be the recommended, first-line treatment approach for symptomatic, recurrent, typical AFL [9, 10].

In recent years, cryoballoon ablation has been developed for AF [11] and has been shown to be non-inferior to RFA in terms of efficacy and safety profile [12]. Cryoballoon ablation is also associated with a shorter learning curve, with more reproducible results across operators and shorter procedure times than RFA, while ensuring a high probability of creating durable PVI [13]. However, the use of cryoballoon PVI only in patients with typical AFL and no prior documentation of AF has not been studied.

## Methods

### Primary endpoint and hypothesis

The primary hypothesis of the CRAFT study is that cryoballoon PVI is superior to CTI ablation as first-line treatment for typical AFL in terms of recurrence of all atrial arrhythmias; it offers the prospect of more complete arrhythmia elimination with a single procedure, while resulting in no increase in procedural risk, or in-catheter laboratory resource utilisation. The primary endpoint is defined as time to first recurrence of sustained (> 30 s) symptomatic atrial arrhythmia, including AF, AFL and atrial tachycardia (AT), following a blanking period of 4 weeks as assessed by implantable loop recorder (ILR) data.

### Secondary endpoints

Key secondary endpoints include (1) time to first episode of AF lasting ≥ 2 min, (2) total AF burden at 12 months, (3) time to recurrence of AFL or AT, (4) procedural and fluoroscopy times and radiation dose and (5) quality of life (QoL) changes at 12 months compared with baseline.

### Safety analysis

The primary safety endpoint is the composite of death, stroke/transient ischaemic attack, cardiac tamponade requiring drainage, atrio-oesophageal fistula, requirement for a permanent pacemaker, serious vascular complications requiring intervention or delaying discharge and persistent phrenic nerve palsy lasting > 24 h. A list of possible procedure-related adverse events is shown in Table 1. A definition of terms is provided in **Supplemental Material**.

**Table 1 Tab1:** Procedure-related adverse events

Air embolism	
Atrio-oesophageal perforation or fistula	
Atrio-septal defect	
Atrioventricular node damage	
Bleedings events, including groin haematoma	
Cardiac or coronary artery perforation	
Death	
Dysphagia	
Major vascular complication	
Myocardial infarction	
Need for unplanned cardiac or vascular surgery	
Pericardial effusion	
Pericarditis	
Persistent or sustained cardiac arrhythmia	
Phrenic nerve paralysis	
Pulmonary vein stenosis	
Site infection from loop recorder insertion	
Stroke or transient ischaemic attack	

### Study design

CRAFT study is an international, prospective, randomized, open with blinded assessment, multicentre superiority study being performed at 12 sites in the UK and Switzerland. The study is funded by Medtronic Saarl Ltd., but the investigators are solely responsible for the study design and conduct, data collection and analyses, manuscript writing and decision to publish. The study has been approved by the ethical review committees at each site. The trial is being conducted in accordance with the principles of Good Clinical Practice and the Declaration of Helsinki. Block randomisation is used to allocate participants in a 1:1 ratio to either:‘Conventional’ treatment with radiofrequency CTI ablation, OR‘Novel’ treatment with cryoballoon PVI

A study flowchart is included for illustration in Fig. 1.

**Fig. 1 Fig1:**
[figure not shown]
Study flowchart for CRAFT

### Participants

The study population consists of patients with persistent AFL in whom the flutter morphology on standard 12-lead electrocardiogram (ECG) is felt to be compatible with typical, CTI-dependent-AFL. Any documentation of previous AF automatically excludes the patient from the study. At minimum, patients were required to have an ambulatory cardiac monitoring or ECGs recorded on at least 3 different dates to exclude AF. Other key exclusion criteria include flutter diagnosed solely on ambulatory Holter, suspected left atrial AFL, prior CTI ablation or PVI, severe left ventricular systolic dysfunction (left ventricular ejection fraction < 30%) and morbid obesity (body mass index ≥ 40). A full list of exclusion criteria is provided in the **Supplemental Material**. A signed, informed consent form is obtained from every participant prior to randomisation.

### Interventions

Ultrasound-guided vascular access and fluoroscopy guidance are recommended for all cases. For participants presenting to the catheter laboratory in AFL, entrainment is performed from the proximal and distal poles of a catheter situated within the coronary sinus, and CTI to confirm the diagnosis of CTI-dependent AFL. Participants found to have non-CTI-dependent AFL or AF at the time of the procedure will be excluded from undergoing the allocated intervention they have been randomised to. Instead, the investigators will be free to offer them ablation treatment appropriate to their arrhythmia.

#### Radiofrequency CTI ablation

In the control arm, the choice of ablation catheter, settings and overall strategy is at the discretion of individual operators. Using fluoroscopy only, the aim is to achieve bidirectional conduction block across the CTI that persists for at least 15 min following the last radiofrequency application, as has previously been described [14, 15].

#### Cryoballoon PVI

A single trans-septal puncture is performed. Routine administration of heparin is used with a target activated clotting time of > 250. The Arctic Front Advance cryoballoon (Medtronic Inc., Minneapolis, USA) and Achieve Advance Mapping catheter (Medtronic Inc., Minneapolis, USA) are employed for all cases. The aim is to achieve a single 180-s ‘effective’ freeze for each pulmonary vein. A freeze is considered ‘effective’ if either of these criteria is met:Time to PVI < 60 s if PV signals are discernible on any pole(s) of the Achieve Advance Mapping catheter, ORIf PV signals not discernible on any pole(s) of the Achieve Advance Mapping catheter, lowering of balloon temperature below − 40 °C at 60 s

In the event that an effective freeze is not achieved at 60 s, the freeze is terminated, and further ablation attempts are made with a better contrast seal. No ‘bonus’ freeze is routinely applied for any PV once an effective freeze has been delivered. In the case of 2 unsuccessful attempts to achieve an effective freeze for any PV, a 240-s freeze is delivered to the vein, followed by an additional 180-s freeze if PVI is not achieved by the former. Failure to achieve PVI with this maximum of 4 freezes is not pursued with further ablation attempts. Targeted treatment of non-PV triggers or use of focal RF catheter as an adjunct is not allowed by the protocol.

Prior to removal of the left atrial catheters, an assessment of each PV is undertaken with the Achieve Advance Mapping catheter. If spontaneous PV reconnection is identified, cryoballoon application is repeated, where required. Participants in persistent AFL will be cardioverted at the end of the procedure. Protamine administration is allowed prior to sheath removal.

#### Implantable loop recorder

The Reveal LINQ (Medtronic Inc., Minneapolis, USA) is implanted according to the manufacturer’s instructions during the ablation procedure. The programmed algorithm for arrhythmia detection is shown in Table 2.

**Table 2 Tab2:** Algorithm for programming LINQ devices

Parameter	Settings
Reason for monitoring	Suspected AF
*Detection*	
Tachy	On
Interval rate	146 bpm
Duration	12 beats
Brady	On
Interval rate	30 bpm
Duration	4 beats
Pauses	On
Duration	3 s
AT/AF detection	AF only
Sensitivity	Less sensitive (nominal)
Ectopy rejection	Nominal
AT/AF recording threshold	All episodes

*AF* atrial fibrillation, *AT* atrial tachycardia, *bpm* beats per minute

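### The loop recorder is set to detect AF only, so regular AFL/AT below 146 bpm has no automatic detection; this chiefly weakens the AFL/AT secondary endpoint, in a direction that favours PVI

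*Protocol article*

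**What the plan says.** Table 2 (Methods, Implantable loop recorder) gives one programme for all devices: "AT/AF detection AF only", AF sensitivity "Less sensitive (nominal"), and a tachycardia detector at "Interval rate 146 bpm" lasting 12 beats.

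The endpoints that use this device are wider than AF. The primary (Primary endpoint and hypothesis) is "time to first recurrence of sustained (> 30 s) symptomatic atrial arrhythmia, including AF, AFL and atrial tachycardia (AT"). The same section has it read from the loop recorder, with the first 4 weeks blanked. A key secondary (Secondary endpoints) is "time to recurrence of AFL or AT". Burden is defined inconsistently: the Abstract names total arrhythmia burden, and the Methods name AF burden.

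The arms treat the flutter circuit differently. In the control arm "the aim is to achieve bidirectional conduction block across the CTI" (Radiofrequency CTI ablation). The Abstract describes the other arm "with patients randomised to PVI not receiving CTI ablation".

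The Follow-up section adds routes other than automatic detection: a symptom diary, participant-activated recordings after symptoms, monthly transmissions, and visits at 3 and 12 months.

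**The concern.** A detector restricted to AF does not match endpoints that count AFL and AT. An AFL/AT episode with regular conduction below 146 bpm meets neither automatic criterion in Table 2, so its capture depends on the participant or on a scheduled contact.

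The gap need not be equal between arms. Everyone is enrolled for presumed CTI-dependent flutter. The control arm aims to block that circuit and the PVI arm leaves it alone. The recurrence the article expects after CTI ablation is AF, which is what the device is set to find. AFL/AT that is missed, or dated late, is therefore expected mainly in the PVI arm. Blinded reading and adjudication cannot restore an episode that was never stored.

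At stake are the comparison of AFL/AT recurrence and, to a smaller extent, the headline hypothesis of superiority for all atrial arrhythmias.

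**Working it through.** **Step 1. The plan's own figure.** Inputs from Sample size calculation: 50% v 25%, two-sided alpha 0.05, power 80%.

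n = [1.96·√(2·0.375·0.625) + 0.8416·√(0.25 + 0.1875)]² / 0.25² = (1.3419 + 0.5567)² / 0.0625 = 57.7, so 58 per group, as stated. Then 116/0.89 = 130.3 against the stated 130. The sample size is not in dispute.

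**Step 2. Which endpoints are exposed.**
- *AFL/AT secondary:* no symptom condition, so a silent slow episode counts and has no automatic route in. Exposed directly.
- *Burden:* if AF burden (Methods) is meant, an AF detector fits. If total arrhythmia burden (Abstract) is meant, it is exposed, because symptom-triggered strips cannot measure burden.
- *Primary:* silent episodes do not count. An event is lost only if it is symptomatic AFL/AT, regular, below 146 bpm, not captured by an activated recording, a monthly transmission or a visit, and the participant has no other captured qualifying episode.

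**Step 3. Size, under assumed rates.** The documents give no ventricular rates, no AFL/AT share and no missed share. Assume equal true 12-month rates of 40%: PVI 25% AF + 15% AFL/AT; CTI 37% AF + 3% AFL/AT, each participant counted under one type. A share m of AFL/AT is missed in both arms, and AF detection is complete.

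Observed rate = AF + AFL/AT × (1 − m).

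Chance of a significant result favouring PVI = Φ[(d − 1.96·SE0)/SE1], where d is the observed CTI rate p₁ minus the observed PVI rate p₂, p̄ is their mean, SE0 = √(2p̄(1−p̄)/58) and SE1 = √([p₁(1−p₁) + p₂(1−p₂)]/58). This uses the two-proportion framework of the plan's sample size as a stand-in for the time-to-event analysis.

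| m | PVI | CTI | d | SE0 | SE1 | Chance |
|---|---|---|---|---|---|---|
| 0 | 40.0% | 40.0% | 0 | – | – | 2.5% |
| 10% | 38.5% | 39.7% | 0.012 | 0.0906 | 0.0906 | 3.4% |
| 20% | 37.0% | 39.4% | 0.024 | 0.0902 | 0.0902 | 4.5% |
| 50% | 32.5% | 38.5% | 0.060 | 0.0889 | 0.0887 | 9.9% |

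**Step 4. If AF is also missed.** Take AF sensitivity as an assumed 90%. At m = 50%: PVI 0.9 × 25 + 7.5 = 30.0%, CTI 0.9 × 37 + 1.5 = 34.8%. The gap falls from 6.0 to 4.8 points and the chance to 7.9%. At m = 20% it is 34.5% v 35.7%, chance 3.4%. At m = 10%, the same missed share as AF, it is 36.0% v 36.0%, chance 2.5%. The distortion of the primary comes from AFL/AT being missed more often than AF.

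**Step 5. The AFL/AT secondary under the same assumptions.** The true excess in the PVI arm is 15 − 3 = 12 points. The observed excess is 12 × (1 − m): 10.8, 9.6 and 6.0 points at m = 10%, 20% and 50%. The ratio of the two rates is unchanged, but the absolute disadvantage of PVI shrinks, and expected events fall from 58 × 0.18 = 10.4 to 5.2 at m = 50%.

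**The case against.** A reader might infer that slow AFL/AT is caught only when the participant has symptoms and transmits, and that the primary comparison is therefore biased toward PVI. The documents do not support that. Monthly transmissions do not depend on symptoms, and there are visits at 3 and 12 months. Participants enter with persistent flutter, so an ongoing recurrence could be seen at a scheduled contact, if late. The primary requires symptoms, and the Follow-up section provides a diary and instructed recordings for that case. AFL/AT at 146 bpm or faster still triggers the device.

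The size is also open to challenge. Steeper inputs, with 20% v 4% AFL/AT and 70% missed, give 26.0% v 37.2% and a chance of about 25%, but nothing in the documents supports them. The PVI-only trial subset in Table 3 reports 10% for all atrial arrhythmias together, though with a different technique and with repeat procedures in more than a third of the PVI arm. Missed AF would work against PVI, as Step 4 shows.

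These objections hold, and they limit the effect on the primary. They do not remove the mismatch for the AFL/AT secondary: scheduled contacts may pick up an ongoing recurrence late, and nothing in the article shows that they recover a silent, self-terminating one.

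**Conclusion.** The mismatch between Table 2 and the endpoints stands, and its expected direction follows from ablating the CTI in one arm only. It falls chiefly on the AFL/AT secondary, and on burden only if the Abstract's wording governs. The primary is exposed only where symptomatic slow AFL/AT escapes activated recordings, monthly transmissions and visits.

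The size cannot be derived from the documents. Under the assumptions of Step 3 the false-superiority chance is about 3.4% to 9.9% for 10% to 50% of AFL/AT missed, against 2.5%, and lower if AF is missed too. For the primary, the missed share must be read as what remains after every capture route. This should be fixed; the evidence does not make it a fatal flaw in the primary comparison.

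**What to change.** - **New implants:** set AT/AF detection to AT and AF in both arms, and have the blinded physiologists review stored AT and tachycardia episodes.
- **Devices already implanted:** apply one reprogramming rule to both arms, log the date for each participant, and report a sensitivity analysis by detection setting. A change during follow-up alters ascertainment over time, which matters for a time-to-first-event endpoint.
- **If the setting cannot be changed:** report the AFL/AT secondary as under-ascertained in a direction favouring PVI, and limit the superiority claim to symptomatic recurrences captured by the recorder as programmed.
- **Wording:** make the Abstract and Methods name the same burden endpoint.

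The cost is more stored episodes, including false positives, for reviewers who already read the transmissions. The documents do not say how specific the AT setting is, so that workload cannot be estimated from them.

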### Follow-up

The study ‘blanking period’ is defined as the initial 4 weeks following ablation. All AADs are discontinued after this period. Cross-overs are not permitted in the blanking period, with the exception of recurrent AFL with 1:1 atrio-ventricular conduction that is resistant to rate control measures. The use of oral anticoagulation is mandated for a minimum of 2 months and subsequently according to individual stroke risk as assessed by the CHA_2_DS_2_-VASc score. Participants are provided with a symptom diary and asked to transmit monthly ECG recordings from their loop recorder. In addition, participants are instructed to record and transmit ECG recordings following arrhythmia-related symptoms. Transmitted data are reviewed regularly by cardiac physiologists who are blinded to the randomisation status. The follow-up duration is 12 months, with planned study visits at 3 and 12 months, when quality of life assessments are performed with the validated EuroQoL EQ-5D-5L questionnaire. Recurrent atrial arrhythmias are treated at the discretion of the responsible clinician. Clinical events will be adjudicated by a panel of cardiologists, who will be blinded to treatment allocation.

### Sample size calculation

In the PReVENT AF study, incidence of AF following CTI ablation for typical AFL was reported in 52% of participants at 12 months follow-up using an ILR [7]. In a meta-analysis by Maskoun et al., the incidence of AF in a similar patient cohort was 45% over a follow-up period of 16 months [16]. However, this included studies with any form of ambulatory ECG monitoring lasting > 7 days. Based on these data, a 50% incidence of atrial arrhythmias following CTI ablation for typical AFL at 12 months is assumed. We anticipate that cryoballoon PVI will reduce the risk of atrial arrhythmias to 25%. Therefore, with an alpha value of 0.05 and power of 80%, the number of participants required to detect a significant difference for a two-sided test is estimated at 58 per group. To cope with a potential loss to follow-up of 11%, a minimum of 130 subjects will be enrolled in the study.

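### The 80% power is calculated for monitoring-detected arrhythmia, while the primary endpoint counts only symptomatic arrhythmia after blanking, so it is not the power of the primary analysis

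*Protocol article*

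**What the plan says.** Under Primary endpoint and hypothesis, the Protocol article defines the endpoint as "time to first recurrence of sustained (> 30 s) symptomatic atrial arrhythmia", covering AF, AFL and AT, "following a blanking period of 4 weeks as assessed by implantable loop recorder (ILR) data". The Abstract carries the same symptomatic restriction. Under Follow-up, symptoms are collected apart from the device's automatic record, by a diary and by patient-initiated transmissions, so the word symptomatic does real work in the definition.

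The Sample size calculation section uses two sources for the control rate. In the first, "incidence of AF following CTI ablation for typical AFL was reported in 52% of participants at 12 months follow-up using an ILR". In the second, a meta-analysis, "the incidence of AF in a similar patient cohort was 45% over a follow-up period of 16 months", with the caveat that "this included studies with any form of ambulatory ECG monitoring lasting > 7 days". It then concludes: "Based on these data, a 50% incidence of atrial arrhythmias following CTI ablation for typical AFL at 12 months is assumed". For the other arm: "We anticipate that cryoballoon PVI will reduce the risk of atrial arrhythmias to 25" per cent. With two-sided alpha 0.05 and 80% power this gives 58 per group, raised to 130 in total for 11% loss to follow-up.

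Neither source rate nor either assumed rate is described as symptomatic, and no step converts one to the other. The primary hypothesis, in the same section as the endpoint, is also worded for atrial arrhythmias without a symptom restriction.

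**The concern.** The document uses two outcomes as though they were one. The hypothesis and the planning rates concern arrhythmia of any kind found by monitoring. The endpoint to be tested is confined to episodes that the patient feels and that occur after the first 4 weeks. A power statement applies only to the outcome whose event rates went into it, so the 80% has not been shown for the primary analysis.

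The reading of the result is at stake. With 58 per group there is little slack: 50% and 25% give just over 80%. If fewer participants meet the symptomatic definition than the planning rates imply, a neutral result could be taken as evidence of no benefit from a trial believed to have 80% power when it had appreciably less.

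**Working it through.** **Inputs from the Protocol article.** Control 50%, PVI 25%, two-sided alpha 0.05, power 80%, 58 per group, 11% loss, 130 enrolled (Sample size calculation); 1:1 allocation; 12 months of follow-up.

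**Input not in the document.** The fraction f of the planned event rate that meets the symptomatic, post-blanking definition. It is an assumption, taken as equal in both arms and shown from 100% to 50%.

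**Step 1: reproduce the plan's figure.** Two proportions, pooled variance, no continuity correction, with p̄ = (p1 + p2)/2:

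n = [1.960·√(2p̄(1−p̄)) + 0.842·√(p1(1−p1) + p2(1−p2))]² / (p1−p2)²

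With p1 = 0.50, p2 = 0.25, p̄ = 0.375: n = [1.960 × 0.6847 + 0.842 × 0.6614]² / 0.0625 = 57.7, so 58 per group, as stated. Allowing for loss, 116/0.89 = 130.3, against 130 stated; the difference is immaterial. The arithmetic is sound.

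**Step 2: power at 58 per group when the rates are 50f and 25f (risk still halved).**

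Power = Φ{[(p1−p2)√n − 1.960·√(2p̄(1−p̄))] / √(p1(1−p1) + p2(1−p2))}

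Example, f = 0.6: p1 = 0.30, p2 = 0.15, p̄ = 0.225. The bracket is 0.15 × 7.616 − 1.960 × 0.5906 = −0.015. Dividing by 0.581 gives −0.026, and Φ(−0.026) = 0.490.

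**Step 3: the same with the planned hazard ratio held, by log-rank.** Under proportional hazards the planning rates imply HR = ln(0.75)/ln(0.50) = 0.415, so |ln HR| = 0.879. For each control rate p1 = 0.50f, the PVI rate is p2 = 1 − (1−p1)^0.415, expected events are d = 58(p1 + p2), and power = Φ(√(d/4) × 0.879 − 1.960) (Schoenfeld).

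Example, f = 0.6: p2 = 0.138, d = 25.4, √(25.4/4) × 0.879 − 1.960 = 0.255, and Φ(0.255) = 0.60.

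| f | Rates, risk halved | Events | Power, two proportions | PVI rate, HR 0.415 | Events | Power, log-rank |
|---|---|---|---|---|---|---|
| 1.0 | 50% vs 25% | 43.5 | 80.2% | 25.0% | 43.5 | 83% |
| 0.9 | 45% vs 22.5% | 39.2 | 73% | 22.0% | 38.8 | 78% |
| 0.8 | 40% vs 20% | 34.8 | 65.5% | 19.1% | 34.3 | 73% |
| 0.7 | 35% vs 17.5% | 30.5 | 57% | 16.4% | 29.8 | 67% |
| 0.6 | 30% vs 15% | 26.1 | 49% | 13.8% | 25.4 | 60% |
| 0.5 | 25% vs 12.5% | 21.8 | 41% | 11.3% | 21.0 | 52% |

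The first row shows that setting proportions against a time-to-event endpoint matters little at the planned rates. The two power columns differ lower down mainly because halving the risk at a lower base rate implies a weaker hazard ratio (0.464 at f = 0.5). A log-rank calculation with risk halved gives about 69%, 52% and 43% at f = 0.8, 0.6 and 0.5.

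**Step 4: no loss to follow-up.** With all 65 per arm, f = 0.8, 0.6 and 0.5 give 71%, 54% and 45% (risk halved) or 78%, 65% and 57% (HR 0.415).

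**Step 5: allowing for AFL and AT.** Suppose, as an assumption, that adding AFL and AT lifts the all-arrhythmia control rate to 60%, with risk halved. Symptomatic shares of 80%, 60% and 50% then give 78%, 59% and 49% at 58 per group. The planned 50% is recovered at a share of 50/60 = 83%; above that, power is at least as stated.

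**The case against.** The strongest reply concerns direction. A reader might infer that the symptomatic rate can only equal or fall below 50%, and that the trial will therefore have fewer primary events than planned. The documents do not support that. The Sample size calculation section describes both source rates as AF, while the endpoint counts AF, AFL and AT. The endpoint is narrower on symptoms and timing but wider on arrhythmia type, so it is not a subset of the source outcome, and Step 5 shows that a full offset is arithmetically possible. Against this, Table 3 lists the same 52% under a column for atrial arrhythmias, and the sample-size paragraph labels its own 50% the same way. On that labelling AFL and AT are already included and there is nothing to offset. The document does not settle which holds.

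A reader might also take the 50% to be a rate of all ILR-detected AF. Only the 52% source is described as using an ILR; the 45% source mixed monitoring methods. Nor does the document say whether either source required symptoms; it only describes neither rate as symptomatic.

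The planned effect was also not the largest available. Table 3 shows 52% versus 12% in PReVENT AF; halving both rates (26% versus 6%) still gives about 84.5% power at 58 per group by the Step 2 formula. That is fair, but the plan chose 50% versus 25%, that trial tested PVI added to CTI ablation rather than in its place, and Table 3 also shows 40% versus 29% in REDUCE AF, for which the same formula gives about 24% before any symptom filter.

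Finally, this is a condensed article, and a fuller protocol may justify the rate. The point does not rest on a missing justification: the paragraph as printed gives 80% power from rates for a differently defined outcome. It is also true that power is a planning figure, and that randomisation, alpha and the validity of the primary test are untouched.

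**Conclusion.** The point stands as a mismatch between the planning rates and the primary endpoint. The calculation of 58 per group is correct for 50% versus 25%, but those rates are for monitoring-detected arrhythmia and the endpoint is symptomatic arrhythmia after blanking. The stated 80% is therefore not the power of the primary analysis.

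The size is conditional. At 58 per group, if 80%, 60% or 50% of the planned events qualify, power is 65.5%, 49% or 41% with risk halved, and about 73%, 60% or 52% with the hazard ratio of 0.415 held. These figures rest on a fraction the document does not give, taken as equal in both arms. A lower event rate is what the symptom filter and blanking would lead one to expect, but it is not proven, because counting AFL and AT may partly offset the loss if the sources counted AF alone. It would go too far to call the trial underpowered by a known amount.

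**What to change.** Rewrite the sample-size paragraph for the endpoint that will be tested. State the assumed 12-month rate of sustained symptomatic AF, AFL or AT after blanking in each arm, the basis for it, and the power at 58 per group. If no basis for a single value exists, give a short table over symptomatic fractions from 50% to 100%, such as the one in the working. Say explicitly that the 50% versus 25% calculation, with its 80% power, refers to all detected arrhythmia irrespective of symptoms, and say whether the source rates are AF only or all atrial arrhythmias, since the paragraph and Table 3 label the 52% differently.

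The cost is one paragraph. Neither the endpoint nor the sample size has to change, and no extra patients are required. The downside is a less favourable stated power for the primary analysis.
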